### Data management

Anonymized TB, HIV, and TB-HIV co-infected patient data obtained from electronic software systems supported by the DoH and clinic-based registers will be collated for quality control and for evaluation of impact made by the intervention in data quality. Also, iDataFax version 2014.1.1 which is clinical data management software will be used for the design of case reporting forms for the HCW interviews and its data entry into the study’s database. Both intervention and control clinics will have data mentoring by the study data management team to ensure that quality of data obtained are improved, standardized, reliable, and valid. The study database files will be password-protected, and access to the files will be limited to authorized study staff members. Quality control measure will be carried out periodically throughout the study period prior to the data analysis.

### Statistical analysis

The primary outcome of mortality and secondary outcomes will be analyzed using cluster-summary methods. The primary outcome will be analyzed among TB-HIV co-infected patients only while the secondary outcomes will be analyzed among TB-HIV co-infected, HIV-only, and TB-only patients. Mortality rate per arm will be calculated as geometric mean of cluster-level summaries and will be compared using unpaired *t* test. The same technique will be applied to secondary outcomes. The *t* test applied in cluster-level summaries is one of the robust methods of analyzing unmatched trials especially when there are small number of clusters per arm [50]. Since we have 16 clusters and 40 sub-clusters, multi-level regression will be used as secondary analyses. Proportional hazard regression with random effects (frailty models) will be used for analyses of time-to-event outcomes. Generalized estimating equations and mixed effects linear models will be used for binary and quantitative outcomes, respectively. These models will take the clustering by PHC supervisor and clinic into account through the random effects. They will also allow us to adjust for baseline variables, especially those with imbalance between arms, as this is likely when clusters are fewer. The HCW interviews will be summarized using descriptive statistics such as means and frequencies. Adjusted baseline descriptive statistics will be calculated as the means of the cluster-level summaries and characteristics of the two arms will be compared using *t* test or rank sum tests. Individual-level summaries at baseline will be compared using *t* test or rank sum tests and Fisher’s exact test. Data will be analyzed with SAS version 9.4 (or higher) (SAS Institute INC., Cary N.C, USA).

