### South African guidelines on TB-HIV integration

The South African Department of Health (SA DoH) has developed guidelines and policies supportive for the integration of TB-HIV services. The key focus areas for TB-HIV integration as standard of care in the most recently updated SA DoH guidelines [8, 12–14] is outlined in Table 1.

**Table 1 Tab1:** Focused areas for TB-HIV integration

▪ Testing and counseling for HIV in all patients with TB. ▪ Intensified case finding for TB in HIV-infected patients. ▪ Isoniazid preventative therapy (IPT) for HIV-positive patients that screen TB negative. ▪ ART initiation for all TB-HIV co-infected patients. ▪ Cotrimoxazole therapy for TB-HIV co-infected patients. ▪ Enhanced retention in care strategies including the post-test counseling and use of community-based outreach workers. ▪ Enhanced ART and TB treatment adherence strategies including the use of community care workers for adherence support and community-based management of selected patients. ▪ A fully integrated data management system—adopting the approach of one patient, one appointment, one file, and one data management system.	

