### Data collection

Data on TB-HIV integration indicators will be obtained from patient files and existing standard customized electronic data management systems supported by SA DoH [4, 41]. Routine clinical information is recorded in paper-based registers and patient clinic folders housed in clinics and subsequently captured onto the relevant TB or HIV electronic system supported by SA DoH. Baseline patient level data will be collected retrospectively for the 12 months prior to study start and will continue prospectively throughout the study period (Tables 2 and 3). In addition, HCW interviews will be conducted, using case report forms, at specific time points during study period from consenting health workers in both the intervention and control clinics. Table 2 summarizes the data to be collected, data source, and outcome measures while Table 3 presents the study’s schedule of activities.

**Table 2 Tab2:** Data collection tools, sources, and outcome measures

Data to be collected	Data source	Outcomes measure
TB-HIV integration indicators		Clinical outcomes
	TIER.Net, community care givers, autopsy reports	- Mortality rates—number of deaths among TB and HIV patients accessing care in study clinics from date clinic enrolled to 18 months post enrolment.
	TIER.Net	- Proportion of patients retained in care—proportion of HIV-infected patients enrolled in care at clinics and alive 12 months.
	TIER.Net	- Viral load testing coverage—proportion of patients on ART with viral loads test done among those eligible for viral load test at requested time points.
	TIER.Net	- Viral load suppression—proportion of patients with undetectable viral load tests among those receiving 12 monthly viral load test.
	TIER.Net and clinic TB registers	- TB treatment outcomes at end of study period— - Cure rates: proportion of new smear-positive patients that are smear-negative in the last month of treatment and on at least one other occasion at least 30 days prior. - Loss to follow-up rates: proportion of new smear-positive patients that interrupted TB treatment for 2 consecutive months or more. - Treatment failure rates: Proportion of new smear-positive patients that are smear-positive at the end of TB treatment period. - Death rate: proportion of new smear-positive patients that died during TB treatment. - Transfer-out rate: proportion of new smear-positive pulmonary TB patients registered that were transferred to another district and for whom the TB treatment outcome is unknown.

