		*Process outcome* - HCT Coverage—proportion of patients with unknown HIV status tested for HIV
	TIER.Net, DHIS and clinic-based registers	
	TIER.Net, DHIS and clinic-based registers	- Co-infection—proportion of TB patients co-infected with HIV
	TIER.Net, DHIS and clinic-based registers	- Time to ART initiation (in days)—time in days between diagnosis of HIV infection diagnosis and ART initiation.
	TIER.Net, DHIS and clinic-based registers	- TB screening coverage among HIV-infected patients— a) Proportion of HIV-infected patients receiving TB screening and b) Frequency of TB screening during follow-up
	TIER.Net, DHIS and clinic-based registers	- IPT initiation— a) Proportion of HIV-infected TB negative patients initiated on IPT and b) Proportion of patients completing IPT course.
	TIER.Net, DHIS and clinic-based registers	- CPT uptake among co-infected patients—proportion of eligible HIV-positive patients initiated on CPT
TB-HIV service integration in the facility macro-environment	Survey instrument developed by Uyei et al. 2014 [7]	Measured TB-HIV integration in terms of: ➢ Organization—such as co-location of services, combined patient records, information management, and joint training ➢ Structure—existent practice of joint service delivery, ➢ Process—behavior and practice of delivering services ➢ Culture—work place culture and personal identification with integrated service delivery
Clinic profile tool aimed at assessing clinics’ infrastructure, capacity, and systems in place to implement TB-HIV integration services	A CAPRISA designed tool	- Resources inventory and needs for implementation of TB-HIV integration services, e.g., available guidelines, protocols, policies, trained staff. - Existing quality improvement interventions, processes and measurements - District level leadership and support
Clinic culture, leadership, resources, etc.	The COACH tool designed by Bergstrom et al. 2015 [56]	- Clinic leadership and support - Staff knowledge and skills - Perceptions of work culture at PHC
Staff Work-related Quality of Life	WHO Work-related Quality of Life Scale	Work-related quality of life for staff at PHC

**Table 3 Tab3:** Study schedule of activities

Study activity	Study time points			
	Baseline (0–1 month)	6–7th month	12–13th month	Monthly (1st–18th month)
Retrospective collection of 12 months data on TB-HIV indicators from TIER.Net*, DHIS** and clinic-based registers	X			
***QI Learning Collaborative (Intervention Clinics Only)	X	X	X	

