### Sample size estimation

We anticipate that about 6000 HIV-positive patients will be diagnosed with active TB in the study population during a 12-month period. This is based on the assumption that between 100 and 200 new TB-HIV co-infected patients are seen in each of the 40 clinics per year. This translates to an average of 350 patients per cluster (assume unequal cluster sizes). Assuming a case fatality rate of 15% in the control arm, coefficient of variation between 0.25 and 0.35, and a type I error rate of 5%, we will have 80% power to detect a 30% reduction in mortality. The chances of detecting other levels of effectiveness are shown in Table 4.

**Table 4 Tab4:** Power to detect different levels of effectiveness (keeping number of events constant)

Reduction in mortality (%)	Power to detect an effect (%)
10	13
20	42
30	80
40	98

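### Primary mortality is compared among patients diagnosed with TB-HIV after randomisation, and the intervention can change who is diagnosed, so case fatality can shift either way with no change in lives saved; viral suppression among the tested has a similar weakness

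*Protocol article*

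**What the plan says.** The Statistical analysis section restricts the primary comparison: "The primary outcome will be analyzed among TB-HIV co-infected patients only". Study outcome measures defines the mortality outcome among people newly diagnosed with TB, HIV or both. Sample size estimation counts the HIV-positive patients expected to receive a TB diagnosis over 12 months, about 6000.

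Table 1 (South African guidelines on TB-HIV integration) lists eight focus areas. They include HIV testing and counselling for all TB patients and "Intensified case finding for TB in HIV-infected patients". The section on training, coaching and mentorship says that the quality improvement teams in intervention clinics work on all eight. The section on the quality improvement intervention names HIV testing coverage among its examples of process improvement. Table 2 (Data collection) lists as a process outcome the "proportion of TB patients co-infected with HIV".

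Table 2 defines viral suppression as the "proportion of patients with undetectable viral load tests among those receiving 12 monthly viral load test". Viral load testing coverage, among patients eligible for the test, is a separate entry.

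The adjustment described in the Statistical analysis section is for baseline variables, in secondary regression models.

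**The concern.** Randomising supervisors balances the clusters and the populations they serve, apart from chance. It does not balance a subgroup that forms later through diagnostic work that one arm is actively promoting. If intervention clinics test and screen more, they may label patients who in control clinics would have stayed TB-only or HIV-only on the register. These patients may be milder than the rest, which lowers case fatality. They may be sicker, for instance ill TB patients newly found to have HIV, which raises it. Neither shift requires a change in the number of deaths.

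Adjusting for baseline variables does not remove this, because the selection arises after baseline. What is at stake is whether a difference in the primary outcome can be read as lives saved, or its absence as no benefit.

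Suppression among the tested has the same structure. If testing coverage differs by arm, so does the group in which suppression is measured.

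**Working it through.** **1. The plan's own power figure.** Inputs from Sample size estimation: "Assuming a case fatality rate of 15% in the control arm", "coefficient of variation between 0.25 and 0.35", 350 patients per cluster, 5% type I error (taken as two-sided), and the claim "we will have 80% power to detect a 30% reduction in mortality". With 16 supervisor clusters there are c = 8 per arm. The unmatched cluster formula is

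power = Φ( √(c−1) × (p0 − p1) / √v − 1.96 ), where v = p0(1−p0)/n + p1(1−p1)/n + k²(p0² + p1²).

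With p0 = 0.15, p1 = 0.105 and n = 350:
- k = 0.25: v = 0.00273, power 62.5%
- k = 0.35: v = 0.00474, power 40.9%

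So 80% is not reproduced with supervisors as clusters. Treating the 40 clinics as clusters (20 per arm, n = 150, k about 0.32) gives 13.5, 43.3, 79.9 and 97.3%, within 2 points of Table 4. That is a separate matter and the present point does not depend on it. The formula is reused in step 4 with the supervisor clusters.

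**2. Who enters each denominator.**
- Statistical analysis: co-infected patients only.
- Study outcome measures: newly diagnosed with TB, HIV or both.
- Table 2: TB and HIV patients accessing care at study clinics.

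The three differ, but all depend on diagnosis or attendance after the trial starts, so none removes the difficulty.

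**3. Effect of case mix alone.** Let f be the extra co-infected patients found, as a share of those who would be found anyway, and r their case fatality. Deaths among the others are unchanged. Then apparent case fatality = (0.15 + f × r) / (1 + f). The article gives neither f nor r; both are assumptions.

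| f | r | Apparent case fatality | Relative change from 15% |
|---|---|---|---|
| 20% | 10% | 0.170/1.2 = 14.2% | −6% |
| 20% | 5% | 0.160/1.2 = 13.3% | −11% |
| 30% | 5% | 0.165/1.3 = 12.7% | −15% |
| 20% | 30% | 0.210/1.2 = 17.5% | +17% |

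To mimic the whole 30% design effect (15% to 10.5%), f = 0.045/(0.105 − r). This is 43% if r = 0 and 82% if r = 5%.

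**4. Chance of a significant result favouring the intervention when no death is averted** (nominal 2.5% in that direction). Put the apparent case fatality in as p1 in step 1, with c = 8 and n = 350:

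| f, r | CV 0.25 | CV 0.35 |
|---|---|---|
| 20%, 10% | 6% | 5% |
| 20%, 5% | 12% | 9% |
| 30%, 5% | 19% | 13% |
| 20%, 30% | 0.1% | 0.3% |

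In the last row the shift works against the intervention and would mask a true benefit.

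**5. Viral suppression, with assumed inputs.** Suppose coverage rises from 60% to 85%, with 85% suppressed among the first 60% and 70% among the added 25%.
- Among the tested: from 85% to (0.60 × 0.85 + 0.25 × 0.70)/0.85 = 0.685/0.85 = 81%.
- Documented suppression among all eligible: from 0.60 × 0.85 = 51% to 0.685, about 69%.

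The two measures move in opposite directions on the same data.

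**The case against.** The size rests on invented inputs. The article gives no baseline testing coverage, detection gain or fatality for extra cases. The 15% figure pairs the favourable ends of both assumed ranges, and mimicking the full target effect takes a very large gain in detection. This is correct, and the figures above are illustrations only.

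A reader might infer that intervention clinics will label more and milder patients, so that the bias favours the intervention. The documents do not support that. Table 2 lists the co-infection proportion as a process outcome without saying that it is expected to move. Control clinics follow the same national guidelines. Table 1 also includes isoniazid preventive therapy, for which the background cites a 37% lower risk of active TB, so the number of co-infected patients could fall instead. The direction is open.

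A reader might also infer that viral load testing is something the intervention targets. It is not among the eight Table 1 areas; it is a listed outcome. Since coverage and suppression among the tested are both reported, their product recovers suppression among all eligible when the two denominators match. This leaves a narrower point: Table 2 words the two denominators differently, and no comparison of the combined measure is stated.

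Partial checks exist. Table 2 includes deaths during TB treatment among new smear-positive patients, a denominator that does not depend on HIV testing. Testing and screening coverage are collected, along with 12 months of pre-study data, so unequal detection could be seen. Seeing it is useful but does not give an unaffected mortality comparison.

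Finally, the analysis plan is not shown and may contain a supportive analysis. The point therefore does not rest on absence. It rests on the denominators that the article itself fixes.

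**Conclusion.** The concern holds as a conditional one. The primary mortality comparison is made in a group formed by diagnosis after randomisation, and the intervention promotes the activities that form it. Case mix can therefore differ between arms and case fatality can move either way with no change in lives saved.

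The size cannot be determined from the document. Under the assumptions shown, the shift runs from 15% down to 12.7% or up to 17.5%, and the chance of a falsely favourable significant result ranges from below the nominal 2.5% to about 19%. The stronger statement, that the trial will show a spurious benefit, does not follow.

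For viral suppression the conclusion is limited: a tested-only figure can mislead if coverage differs by arm. The primary analysis need not be replaced, but on its own it is not enough to support a claim about lives saved.

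**What to change.** 1. Keep the primary analysis. Add a prespecified supportive analysis, by the same cluster-level method, of all-cause mortality to 18 months in all patients on each clinic's HIV and TB registers at clinic enrolment. Use all-cause deaths, since counting only TB-HIV deaths would bring the diagnostic label back in.
2. Report the number of co-infection diagnoses by arm, with severity at diagnosis where recorded, and interpret the primary result in that light. Do not require the two analyses to agree in direction: with 16 clusters and fewer deaths, such a rule could block a real benefit by chance.
3. Report viral suppression among all patients eligible for a test, counting the untested as not documented suppressed, with the tested-only figure as secondary.

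The cost is modest. The article already plans to obtain data on all TB, HIV and co-infected patients in the 40 clinics, with 12 months of retrospective data and monthly downloads. This assumes that the anonymised records allow registered patients to be followed across downloads. The downside is that the registered cohort has lower mortality, leaves out newly diagnosed patients and answers a slightly different question, so it is supportive only.

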### Study setting and design

This is an open-label cluster randomized controlled trial where the cluster is defined as the group of clinic(s) under the same PHC clinic supervisor, where each of the 16 PHC clinic supervisors may oversee between 3 and 5 PHC clinics. Cluster randomization was chosen for practical reasons because the study will be carried out in pragmatic settings involving 40 PHC clinics within the King Cetshwayo district (formerly called uThungulu) [34] and Ugu districts in KwaZulu-Natal, South Africa. A total of 11.1 million people (19.9% of the South African population) live in KwaZulu-Natal [35]. The province has the highest TB-HIV disease burden in South Africa with an estimated TB-HIV co-infection rate of 70% [12, 36]. The two districts were selected because they are rural with high burden of TB, HIV, and TB-HIV co-infection, despite TB and HIV treatment services in accordance with current guidelines being available [13, 14, 37]. In 2016, 82.3% of TB-HIV co-infected patients were initiated on ART in KwaZulu-Natal, slightly lower than the national ART initiation rate of 84.5% [38]. King Cetshwayo district, located on the northern coast of KwaZulu-Natal, has a population of 937,793, with approximately 80% living in rural settings [39]. Similarly, Ugu district, situated in southern KwaZulu-Natal has 86% of its population of 750,214 living in rural areas [38, 40]. The in-hospital case fatality rate due to TB-HIV co-infection in both King Cetshwayo district (38.4%) and Ugu district (38.8%) remains high despite ART availability [27]. In 2015, over a quarter of all deaths in KwaZulu-Natal, irrespective of age or gender, were caused by TB (15.5%) or HIV (12.2%). PHC clinics offer community level frontline services and chronic care for all health ailments, including TB and HIV. Patient level data for these diseases are routinely captured electronically [41].

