### Randomization and study groups

Randomization will occur at the level of the PHC supervisor. This is being done to avoid contamination of intervention effects into control clinics since each supervisor routinely supports multiple clinics. Each PHC clinic supervisor will be randomly assigned in a 1:1 ratio to the intervention or control arm. The study investigators would provide a list of facilities and supervisors to be randomized using a computer-generated randomization list generated by study statistician. In South Africa, a PHC clinic supervisor fulfills a management role at PHC clinics [42], and are mandated to ensure smooth clinic operations through oversight of clinic performance against set targets including patient clinical outcomes and programme performance targets, and oversees the implementation of clinical guidelines. Each PHC clinic supervisor may oversee between three and five PHC clinics within one district. Therefore, through randomization of 14–16 PHC clinic supervisors working in both the Ugu district and King Cetshwayo district, 40 clinics (20 in each arm) will be enrolled into this study as each supervisor oversees on average three to five medium-sized clinics. Not all clinics under the purview of the PHC clinic supervisors randomized will be enrolled into the study. Clinics will be excluded if ART services are not offered on site, services are run by a single nurse, and if they are mobile clinics or clinics located within hospitals. All eligible clinics enrolled in the control arm of this trial will receive the prevailing standard-of-care for TB-HIV integration (Fig. 2) in accordance with the DoH guidelines. While the study team will not interfere with any additional benefit that control clinics may receive (for example, support from other NGOs), changes to the background standard of care will be recorded systematically and accounted for in the final analysis.

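### The primary mortality test is valid but ignores baseline data already being collected; cluster-level baseline adjustment is a cheap improvement whose gain depends on a correlation the article does not give

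*Protocol article*

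**What the plan says.** All references are to the protocol article.

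- **Primary test** (Statistical analysis): "Mortality rate per arm will be calculated as geometric mean of cluster-level summaries and will be compared using unpaired" *t* test. The stated reason is robustness in unmatched trials with few clusters per arm. No baseline term is named.
- **Adjustment** (same section): multi-level models are planned, as secondary analyses. Of these it says: "They will also allow us to adjust for baseline variables, especially those with imbalance between arms, as this is likely when clusters are fewer".
- **Baseline data** (Data collection): "Baseline patient level data will be collected retrospectively for the 12 months prior to study start". Table 2 lists mortality among the TB-HIV integration indicators, and Table 3 schedules retrospective collection of 12 months of those indicators. A baseline mortality rate per cluster is therefore obtainable, though the article never names one.
- **Clusters** (Study setting and design): "the cluster is defined as the group of clinic(s) under the same PHC clinic supervisor, where each of the 16 PHC clinic supervisors". Randomization and study groups gives the count as "through randomization of 14–16 PHC clinic supervisors", with each supervisor "randomly assigned in a 1:1 ratio to the intervention or control arm".
- **Size** (Sample size estimation): "about 6000 HIV-positive patients will be diagnosed with active TB in the study population during a 12-month period", and "This translates to an average of 350 patients per cluster (assume unequal cluster sizes".

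**The concern.** With about eight supervisors per arm, lasting differences in mortality between supervisors' clinics pass straight into an unadjusted effect estimate. They widen its standard error, and in any one allocation they can favour one arm by chance. The plan foresees such imbalance but deals with it only in secondary models, where covariates may be chosen partly on the imbalance seen. A baseline value of the primary outcome is the natural covariate, and its source data are already scheduled. At stake is the precision of the primary result and how credible it looks if the arms differed before the study began.

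**Working it through.** **Inputs from the article.** 16 clusters, so c = 8 per arm; m = 350 per cluster (6000/16 = 375 changes power by at most 1 point); control fatality 15%; 30% reduction, so 10.5%; coefficient of variation k = 0.25 to 0.35; type I error 5%.

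**Assumptions.** Two-sided test; log scale (implied by geometric means); equal cluster sizes; 350 patients per cluster in the baseline year too; and a correlation between years, which the article does not give.

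**1. The plan's own figure.** The article states 80% power for a 30% reduction. With 8 per arm this is not reached within its range of k; it would need k of about 0.19 to 0.21. That is a separate problem with the power statement. Here it only fixes the starting point.

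**2. Variance of a cluster's log rate:** k² + (1 − p)/(mp).

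- Binomial part, control: 0.85/52.5 = 0.0162. Intervention: 0.895/36.75 = 0.0244.
- Between-cluster share at k = 0.25: 0.0625/0.0787 = 79% (control), 0.0625/0.0869 = 72% (intervention).
- At k = 0.35: 0.1225/0.1387 = 88% and 0.1225/0.1469 = 83%.

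Most of the variance is thus of the kind that a stable baseline rate could explain.

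**3. Unadjusted power.** Worked at k = 0.30: SE = √[(0.1062 + 0.1144)/8] = 0.166; ln 0.7 = −0.357; noncentrality 0.357/0.166 = 2.15 on 14 df; power 52%. The same steps give 64% at k = 0.25 and 42% at k = 0.35.

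**4. Adjusted power.** With within-arm observed correlation r, the error variance is multiplied by (1 − r²), and estimating the slope costs on average a factor 13/12, with 13 df. Leaving aside the lost degree of freedom, break-even is (1 − r²) × 13/12 = 1, so r² = 1/13 and r = 0.28. Below that, adjustment loses a little. At k = 0.30 and r = 0.5: 2.15/√(0.75 × 13/12) = 2.38, power 60%.

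The observed r is lower than the correlation of the true rates, because 52.5 expected deaths per cluster carry binomial noise. In control clusters this caps r at about 0.79 (k = 0.25) to 0.88 (k = 0.35) even if the true rates never changed.

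**5. Simulation with noise in both periods** (log-normal cluster effects, binomial deaths, 100,000 trials per setting). Power in %, with the change from unadjusted in points:

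| True year-to-year correlation | k = 0.25 | k = 0.30 | k = 0.35 |
|---|---|---|---|
| Unadjusted *t* test | 64 | 52 | 43 |
| Adjusted, 0 | 60 (−4) | 49 (−3) | 40 (−3) |
| Adjusted, 0.3 | 62 (−1) | 51 (−1) | 43 (−1) |
| Adjusted, 0.5 | 67 (+3) | 56 (+4) | 47 (+4) |
| Adjusted, 0.7 | 74 (+10) | 65 (+13) | 57 (+14) |
| Adjusted, 0.8 | 80 (+16) | 72 (+20) | 65 (+21) |

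Type I error (k = 0.30, correlation 0.7) is 5.0% for both tests.

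**6. Chance imbalance.** Under simple 1:1 allocation the difference in mean baseline log rate has SD √(2 × variance/8), which is 0.140, 0.163 and 0.186 at the three values of k. It exceeds 0.15 (0.15/0.357 = 42% of the target effect) in about 28%, 36% and 42% of allocations.

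**7. Is the baseline value like for like?** Table 2 takes mortality from TIER.Net, community caregivers and autopsy reports, up to 18 months after clinic enrolment. The retrospective row of Table 3 covers 12 months and lists TIER.Net, DHIS and clinic registers. So the baseline window is shorter and two death sources are not listed for it. Under Data management, both arms also receive data mentoring during the study, which may change how deaths are recorded. As an illustration, if only half of baseline deaths were recorded, evenly across clusters, the gain at correlation 0.7 falls from 10–14 to about 7–10 points, and at 0.8 from 16–21 to about 11–17.

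**The case against.** The case for leaving the plan alone is substantial. An unpaired *t* test on cluster summaries holds its type I error, the article gives a sound reason for it, and baseline adjustment is already planned as a secondary analysis. The dispute is only over which analysis is primary. All of that stands, and it is why this is not an error.

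Three stronger readings are tempting, and the article does not support them:

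- **That adjustment recovers much of the power missing from 80%.** At k = 0.30 the shortfall is 28 points. A correlation of 0.5 returns 4 of them, 0.7 returns 13 and 0.8 returns 20; at 0.3 or below there is no gain. No passage says which applies, and the differences in death sources and recording could push the correlation down.
- **That allocation was unstratified.** The article mentions only 1:1 allocation from a computer-generated list. A condensed article may omit stratification, so the imbalance figures in step 6 are conditional on simple randomization.
- **That adjustment repairs the sample size section.** It does not; the 80% claim has to be reconciled with 16 supervisor clusters in its own right.

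Timing also counts. Data collection is ongoing in an open-label trial with monthly downloads, so a change of primary analysis needs safeguards.

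Against this, the secondary models do not fully replace the proposal. The article prefers cluster-level methods because clusters are few, and a cluster-level regression stays within that approach. It also fixes one covariate in advance.

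**Conclusion.** The point holds as an efficiency and robustness improvement. The primary test is valid but leaves unused a baseline measure whose data are being collected, in a design where the plan itself expects imbalance. The trade is a loss of at most about 4 points of power if cluster mortality is unrelated from year to year, against a gain of about 10 to 21 points if the true correlation is 0.7 to 0.8. Between 0.3 and 0.5 the effect runs from slightly negative to slightly positive.

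These figures rest on 8 clusters per arm, equal cluster sizes, comparable death recording in both years and the article's k of 0.25 to 0.35. With 14 supervisors, the lower count given, unadjusted power falls to about 56%, 45% and 36%, and the adjusted test has 14 − 3 = 11 df. The correlation is unknown, so the size of the gain cannot be promised.

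**What to change.** By a documented amendment made before any comparison of outcomes by arm:

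1. Make the primary analysis a cluster-level linear regression of log mortality on arm and the same supervisor cluster's log mortality in the 12 months before study start, testing arm on 13 df (16 clusters).
2. Compute the baseline rate in TB-HIV co-infected patients, from death sources available in both periods (TIER.Net and clinic registers), and state how its 12-month window relates to the 18-month outcome window.
3. Keep the unadjusted *t* test as a sensitivity analysis.
4. Describe the expected gain as conditional on the correlation, and handle the 80% power statement separately.

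**Cost:** one degree of freedom, a possible loss of 3 to 4 points of power if the correlation is nil, the amendment, and some work to define a comparable baseline rate. No new data source is needed.
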